## Figures and Tables

**Figure 1 cmtr-19-00017-f001:**
[figure not shown]
Planned patient flow.

**Table 1 cmtr-19-00017-t001:** Current participating sites.

Name	Country
Uniklinik RWTH Aachen, Aachen	Germany
Charité—Universitätsmedizin Berlin, Corporate Member of Freie Universität Berlin and Humboldt-Universität zu Berlin, Department of Oral and Maxillofacial Surgery, Berlin	Germany
Hannover Medical School	Germany
University Hospital Heidelberg	Germany
University Hospital Leipzig	Germany
LMU University Hospital, Munich	Germany
University Hospital Tübingen	Germany
Military Hospital Ulm	Germany
Shimane University Hospital, Izumo	Japan
Erasmus University Medical Centre, Rotterdam	The Netherlands
Instituto Português de Oncologia de Lisboa, Lisbon	Portugal
12 de Octubre University Hospital, Madrid	Spain
Uppsala University Hospital, Uppsala	Sweden
University Hospital Basel, Basel	Switzerland
University of Illinois Hospital (UIHealth), Chicago	USA
Tarrant County Hospital, Fort Worth	USA
University of Florida College of Medicine, Jacksonville	USA
Mount Sinai Hospital, New York	USA

**Table 2 cmtr-19-00017-t002:** Inclusion and exclusion criteria.

Inclusion Criteria	Preoperative Exclusion Criteria	Additional Exclusion Criteria
- Age 18 years and older - Patients undergoing reconstruction of mandibular defects of ≥2 cm in size following segmental resection of pathologic mandibles due to oral tumours (including OSCC, osteosarcoma, and ameloblastoma), medication-related osteonecrosis of the jaw associated with bisphosphonates or immunomodulatory agents, or metastatic disease from primary sites, such as the lung, breast, prostate, liver or kidney - Intention to undergo mandibular reconstruction with autologous bone using a primary (one-stage) or secondary (two-stage) approach - Informed consent obtained according to IRB/EC procedures	- Tumours affecting the condyle - Patients under palliative care - Previous extensive mandibular surgeries (including reconstructions, e.g., TMJ replacement) that may potentially confound the outcome measures	- No osseous reconstruction with autologous bone performed within 18 months of resection

EC, ethics committee; IRB, investigational review board; OSCC, oral squamous cell carcinoma; TMJ, temporomandibular joint.

**Table 3 cmtr-19-00017-t003:** Data collection at each visit.

Assessment Parameters	Pre-, Intra-, and Postoperative Visits *									
	Visit 1	Visit 2	Visit 3	Visit 4 *	Visit 5 *	Visit 6 *	Visit 7 *	Visit 8 *	2nd Stage Recon	Post 2nd Stage Reconstruction Visits ^1^
	Screening/Preoperative	Intraoperative (Day 0)	Discharge	3 Months (±2 Weeks)	6 Months (±1) Month	12 Months (±2) Months	18 Months (±2) Months	2 Years (±3) Months	Intraoperative (Day 0′)	3 Months (±2 Weeks) 6 Months (±1) Month 12 Months (±2) Months 18 Months (±2) Months 2 Years (±3) Months
**Patient information/consent**	X									
**Eligibility**	X									
**Baseline characteristics**	X									
**Tumour/osteonecrosis of mandible characteristics**	X									
**Adjuvant treatment for the malignant conditions (OSCC, Osteosarcoma of mandible, Malignant ameloblastoma, Oral metastases) ^2^**			X							
**Surgical parameters**										
**Resection**		X								
**Osseous reconstruction ^3^**		X							X	
**Additional surgeries ^4^**				X	X	X	X	X		X
**Pathological assessment**			X							
**Clinical outcomes**										
**Neurological function**	X		X	X	X	X	X	X		X
**Dental status**	X		X		X	X	X	X		
**Dental rehabilitation**				X	X	X	X	X		X
**Survival**		X	X	X	X	X	X	X	X	X
**Patient-reported outcomes**										
**OHIP**	X		X	X	X	X	X	X		X
**EQ-5D-5L**	X		X	X	X	X	X	X		X
**Patient satisfaction**					X	X	X	X		X
**Adverse events**		X	X	X	X	X	X	X	X	X
**Radiological assessment ^5^**	X	X	X	X	X	X	X	X	X	X

* Postoperative FU visits with the defined time windows are calculated from the day of mandibular resection (i.e., day 0) and reconstruction (if the patient undergoes primary reconstruction).^1^ Post-second-stage reconstruction visits will be calculated from the day of secondary reconstruction (day 0). Patients will be followed up for a maximum of 2 years from the time of mandibular resection. ^2^ Information on adjuvant treatment for the malignant conditions may be available at a different timepoint and will be documented whenever it becomes available. ^3^ Osseous reconstruction can occur on the day of resection (one-stage reconstruction) or on a different day (two-stage reconstruction). ^4^ Additional surgeries may occur at any time after mandibular resection. ^5^ All images will be taken according to the local standard of care and will be collected. Assessments will be performed on available images.

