Many clinical questions remain in the present clinical landscape. These include the known limitations of donor sites; specifically, it is unclear how donor site morbidity influences the prolonged rehabilitation of patients undergoing reconstruction following segmental mandibular resection. Further, it is unclear whether the QoL of patients undergoing two-stage reconstruction is improved if a longer rehabilitation process is avoided. The primary endpoint of a reconstruction should be the ability to offer all patients a dental rehabilitation protocol, yet in the present treatment environment, only 15–20% of SMDR patients receive dental implants [8,9,10,11,12]. Moreover, mandibular reconstruction following tumour/mandibular resection poses notable challenges for treatment outcomes, particularly due to limitations inherent in both one-stage and two-stage osseous reconstruction techniques. One-stage reconstruction enables faster restoration but may result in suboptimal outcomes due to intraoperative difficulties in accurately contouring the graft, especially in complex defects, leading to impaired dental rehabilitation, aesthetic compromise, and increased flap failure risk. Two-stage reconstruction facilitates more effective treatment planning for complex defects and allows a period of bone adaptation before the final reconstruction but delays rehabilitation, increases infection and scarring risks, and often requires multiple interventions, adversely affecting recovery and overall clinical outcomes. Another aspect of this study will be to investigate the extent to which the principal goal of mandibular bone reconstruction can be realised and the cumulative surgical, prosthodontic, and logistical demands involved before achieving functional or even theoretically viable dental rehabilitation. This study has a two-year follow-up period; although it may not be sufficient to evaluate long-term outcomes, it will allow assessment of whether the reconstruction can be used for a dental implant and dental rehabilitation protocol. Any such dental rehabilitation should ideally take place within a time period of up to two years after the segmental defect reconstruction.

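### Table 3 schedules visits to 2 years after second-stage reconstruction, but its footnote ends follow-up 2 years after resection, so two-stage patients have only 6 to under 24 months after reconstruction

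*Protocol article*

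**What the plan says.** The points below are all in the protocol article.

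- **Schedule.** The last column of Table 3 lists the visits after second-stage reconstruction as "3 Months (±2 Weeks) 6 Months (±1) Month 12 Months (±2) Months 18 Months (±2) Months 2 Years (±3) Months".
- **Clock for those visits.** Footnote 1 to Table 3: "Post-second-stage reconstruction visits will be calculated from the day of secondary reconstruction (day 0").
- **Cap.** The next sentence of the same footnote: "Patients will be followed up for a maximum of 2 years from the time of mandibular resection".
- **Clock for Visits 4 to 8.** The asterisked note: "Postoperative FU visits with the defined time windows are calculated from the day of mandibular resection (i.e., day 0) and reconstruction", the latter when reconstruction is primary. For one-stage patients the two clocks coincide.
- **Latest reconstruction.** Table 2 excludes patients under the heading "No osseous reconstruction with autologous bone performed within 18 months of resection". Section 2.11 uses the same 18-month limit to define who is analysed.
- **Time horizon.** The Discussion states a two-year follow-up period, says it will show whether the reconstruction can serve implants and dental rehabilitation, and adds: "Any such dental rehabilitation should ideally take place within a time period of up to two years after the segmental defect reconstruction".
- **Analysis.** Section 2.11 defines no primary or secondary outcomes. It plans descriptive summaries, including by treatment pattern, and adverse event rates whose denominator is the whole population regardless of dropout.

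**The concern.** Two adjacent sentences of one footnote set different end points for the same patients. A site with a two-stage patient cannot both stop at 24 months from resection and hold a visit 24 months after a later operation.

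The consequence goes beyond scheduling. Implant placement, time to function, graft loss, non-union and loss of implants in the reconstructed segment can arise only after osseous reconstruction. If one group is watched for 24 months after that operation and the other for as little as 6, a crude percentage by treatment pattern mixes the effect of treatment with the length of observation. The Introduction and Discussion both name one-stage versus two-stage surgery as an open question, so readers are likely to make that comparison.

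**Working it through.** The document gives no sample size or power figure to reproduce; the check is calendar arithmetic.

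**Inputs**
- Cap: 24 months from resection (Table 3, footnote 1).
- Gap t from resection to second-stage reconstruction: 0 < t ≤ 18 months (Table 2; section 2.11).
- Post-second-stage visits v with windows w, in months: 6 ± 1, 12 ± 2, 18 ± 2, 24 ± 3, and 3 months ± 2 weeks (Table 3).

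**Step 1: follow-up available after reconstruction.** This is 24 − t.
- One-stage (t = 0): 24 months.
- t = 3: 24 − 3 = 21.
- t = 6: 24 − 6 = 18.
- t = 12: 24 − 12 = 12.
- t = 18: 24 − 18 = 6.

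**Step 2: which visits fit.** At its nominal date a visit fits if t ≤ 24 − v. At the earliest date in its window it fits if t ≤ 24 − v + w. If the cap is also stretched to 27 months by the +3-month window of Visit 8, it fits if t ≤ 27 − v + w.

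| Post-second-stage visit | Nominal | Early window | Early window, cap 27 |
|---|---|---|---|
| 12 months | t ≤ 12 | t ≤ 14 | t ≤ 17 |
| 18 months | t ≤ 6 | t ≤ 8 | t ≤ 11 |
| 2 years | t ≤ 0 (none) | t ≤ 3 | t ≤ 6 |

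The 3- and 6-month visits fit nominally for every permitted gap (24 − 6 = 18).

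**Step 3: follow-up needed to honour the schedule.** The last visit falls at t + 24 months from resection. At t = 18 that is 42 months (±3), against a stated maximum of 24.

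**Step 4: illustration of the possible distortion.** The documents give 15–20% for dental rehabilitation or implants, without a time horizon. Assume that this is reached 24 months after reconstruction, at a constant hazard, and is the same in both groups. With p the 24-month proportion, h = −ln(1 − p)/24 and the observed proportion is 1 − exp(−h(24 − t)) = 1 − (1 − p)^((24 − t)/24).

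| Gap t (months) | Exponent | p = 20% | p = 15% |
|---|---|---|---|
| 6 | 0.75 | 15.4% | 11.5% |
| 12 | 0.50 | 10.6% | 7.8% |
| 18 | 0.25 | 5.4% | 4.0% |

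The hazard shape, the 24-month horizon and the gaps are assumptions. Only the unequal follow-up in steps 1 and 2 comes from the protocol.

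**The case against.** The best defence is that the second sentence of footnote 1 truncates the first: visits are counted from the second operation and simply stop at the cap. That reading is possible, and Figure 1, which is not available here, might support it. It makes the 3- and 6-month visits feasible for everyone and the 12- and 18-month visits feasible for shorter gaps. But it leaves the 2-year entry unattainable at its nominal date, and it leaves the unequal observation as it is.

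Several stronger readings are tempting and are not supported.

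- A reader might infer that no two-stage patient can ever supply a 2-year visit. The visit windows allow it when the gap is 3 months or less, or 6 months on the most lenient reading.
- A reader might infer that the registry commits itself to a 2-year post-reconstruction endpoint. It designates no outcomes, and the Discussion's two-year horizon describes when rehabilitation should ideally occur. The Discussion also concedes that follow-up may be too short for long-term outcomes.
- A reader might infer that two-stage surgery will look worse purely through truncation. No formal comparison is fixed, and summaries at matching post-reconstruction visits would avoid most of the problem. Counted from resection, both groups share a 24-month horizon, and later rehabilitation would then partly be a real effect of delay.
- A reader might expect fewer adverse events overall in two-stage patients. Collection starts at enrolment and includes first-stage events, so the concern is confined to events that follow osseous reconstruction.
- A reader might take the empty cell for "Dental status" in the post-second-stage column as a lost outcome. It remains scheduled at Visits 5 to 8, which are anchored on resection, and nothing says these stop after the second operation.

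The choice of analysis method can reasonably be left to an analysis plan that is not shown. That plan cannot recover data that were never collected, and it cannot tell sites which sentence of the footnote to follow.

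**Conclusion.** The point stands as an inconsistency in stated text with a practical consequence. Two-stage patients have 24 − t months of post-reconstruction follow-up, between 6 and just under 24, against 24 in one-stage patients. The 2-year post-second-stage entry fits no two-stage patient at its nominal date. The Discussion's statement about assessing dental rehabilitation holds in full only for one-stage patients.

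Summaries of post-reconstruction rehabilitation, graft and implant events by treatment pattern could understate these events in two-stage patients. The adverse event denominator makes no allowance for differing observation time. The size is unknown, because the documents give neither the distribution of gaps nor the timing of events; the percentages in step 4 are illustrative only.

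For an exploratory registry without designated outcomes this should be fixed, but it is not a fatal flaw.

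**What to change.** Reconcile the two sentences of footnote 1 in one of two ways.

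1. **Keep the cap.** State that post-second-stage visits take place only until 24 months after resection, remove the 2-year post-second-stage entry, and limit the Discussion claim accordingly. The 12- and 18-month entries can stay, since they are reachable for shorter gaps. This costs wording only.
2. **Keep the schedule.** Correct the cap so that two-stage patients are documented until 2 years after reconstruction. This means up to 42 months from resection, or 42 − 24 = 18 months more than now, across 18 sites. It would bear on the analysis planned for May–September 2026, so it is not clearly cheap. Enrolment stood at 138 of a planned 300, so an amendment could still reach most patients.

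Under either option, measure dental rehabilitation, graft and implant outcomes from the date of osseous reconstruction, censor at the end of follow-up, and compare one-stage and two-stage patients only over post-reconstruction time that both groups reach. Under the cap, that is 6 months if every two-stage patient is to be covered. Any longer comparison rests on patients with shorter gaps and should say so. The dates of reconstruction and implant placement are already collected (sections 2.5.2 and 2.9.1), so this needs analysis wording and no new data items.

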## Data Availability

No data were generated or analyzed in this article, as this article describes a study protocol.

## Abbreviations

The following abbreviations are used in this manuscript:

AE	Adverse event
EC	Ethics Committee
EQ	EuroQoL
IRB	Investigational Review Board
OHIP	Oral Health Impact Profile
OSCC	Oral squamous cell carcinoma
QoL	Quality of life
SAP	Statistical analysis plan
SMDR	Segmental mandibular defect reconstruction
TMJ	Temporomandibular joint
TNM	Tumour, node, metastasis
VSP	Virtual surgical planning
